### Procedures

#### Recruitment, informed consent and data collection

##### Pre-study evaluation of ReachNow detection tool

To recruit families, outreach staff will be trained to use an adapted version of ReachNow, a proactive community case detection tool (van den Broek et al., 2023). The proactive case detection approach employs illustrated vignettes depicting a family experiencing multiple psychosocial challenges (including mental health difficulties, family conflict and financial stress). The simple decision algorithm asks outreach staff to assess whether the depicted family resembles families they know in their community who might benefit from focused mental health support. If they identify similarities, they are prompted to refer those families for assessment. Previous versions of the child-focused tool demonstrated 70% accuracy compared to clinical assessment in Sri Lanka and Palestine (van den Broek et al., 2021, 2023). The family-adapted version was piloted in Jordan during the feasibility study with 78 families, demonstrating feasibility and appropriateness. In the present study, the tool will be formally evaluated for accuracy.

War Child Jordan will identify and train outreach staff on the participant inclusion/exclusion criteria and how to use the family version of the ReachNow detection tool to identify families who are eligible for the intervention. These individuals are trusted and respected community members who have established and regular communication with families who are struggling, including personnel and volunteers. During outreach for study enrolment, the family version of the ReachNow tool will be evaluated for accuracy by comparing the ReachNow caseness with screening outcomes assessing mental health challenges (caregiver and child), family functioning difficulties, parenting challenges and financial stress in accordance with study inclusion criteria.

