#### Primary implementation hypotheses

The ReachNow tool will accurately identify 70% or more of families in need of focused mental health support as identified through screening results. In addition, the FamilyACT tool will demonstrate adequate reliability and validity for assessing facilitator competencies in delivering family-systemic interventions in humanitarian settings.

The study will secondarily explore mechanisms of change of the intervention through mixed-methods exploratory longitudinal analyses.

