##### Recruitment

Recruitment will be led by outreach staff under the supervision of War Child Jordan during the study enrolment period using the family version of the ReachNow detection tool. Outreach staff will contact families who meet the eligibility criteria, inform them about the intervention using a script and offer an invitation to participate. Those families who confirm interest will be asked for verbal consent and then referred to the research team for the screening assessment.

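### ReachNow users are trained on, and contact families by, the eligibility criteria that define its reference standard, so the confirmed share (PPV) would describe the tool plus a pre-filter

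*Protocol article*

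**What the plan says.** All of the following is in the protocol article.

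- **Hypothesis**: the stated expectation is that "The ReachNow tool will accurately identify 70% or more of families in need of focused mental health support as identified through screening results" (section *Primary implementation hypotheses*).
- **Index test** (*Pre-study evaluation of ReachNow detection tool*): illustrated vignettes and a decision rule. "The simple decision algorithm asks outreach staff to assess whether the depicted family resembles families they know in their community"; a match prompts referral for assessment. The eligibility criteria are not described as part of the rule.
- **Users** (same section): the sponsor's local team will "identify and train outreach staff on the participant inclusion/exclusion criteria and how to use the family version of the ReachNow detection tool".
- **Timing** (same section): "During outreach for study enrolment, the family version of the ReachNow tool will be evaluated for accuracy". No phase or subset is described in which the tool is used by staff without criteria training.
- **Reference standard** (same section): screening outcomes on caregiver and child mental health, "family functioning difficulties, parenting challenges and financial stress in accordance with study inclusion criteria". *Implementation tool evaluation* names the screening results as the standard for sensitivity, specificity, PPV and negative predictive value.
- **Route to screening** (*Recruitment*): "Outreach staff will contact families who meet the eligibility criteria". Those who are interested and consent verbally are then referred to the research team.
- **Who screens** (*Screening*): trained research assistants, using the K10, the caregiver-report SDQ and structured questions.
- **Meaning of the 70% in previous studies** (Table 3): about 70% of children identified by the child-focused tool were confirmed in need on clinical assessment. That is a PPV.

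**The concern.** The people who apply the index test are taught what makes a family reference-positive. Read literally, the Recruitment section then has them select on it before verification. A family that matches the vignette but seems not to meet the criteria is not contacted and not screened, and so cannot appear as a false positive. The resulting figure describes tool, criteria training and pre-selection together, whereas the article describes the tool as a vignette and decision rule.

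This matters because ReachNow accuracy is a primary implementation hypothesis with a fixed 70% mark, and the impact statement presents the tools as validated resources for immediate adoption. An organisation that adopts only the vignette and rule could see a lower confirmed share than the trial reports. The selection cannot be undone later: if the vignette decision for non-referred families is not recorded, it is lost. The trial's effectiveness analyses are not affected.

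**Working it through.** **Nothing to reproduce.** The 70% is a target. The article gives no sample size, precision or two-by-two counts for this evaluation. The check therefore concerns direction and plausible range, and every numerical input except the 70% is an assumption.

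**Step 1: direction for PPV.** Let p be the PPV of the vignette decision alone. Suppose staff then keep a fraction Se of the truly eligible vignette-positive families and drop a fraction Sp of the ineligible ones, where the filter is conditionally independent of the vignette result. Then

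PPV odds with filter = p/(1−p) × LR+, where LR+ = Se/(1−Sp).

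PPV rises whenever LR+ exceeds 1, and is unchanged when LR+ = 1 (a filter carrying no information).

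**Step 2: range under assumed filters.**

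| Tool-only PPV (odds) | Weak filter: Se 0.90, Sp 0.20, LR+ 1.125 | Moderate filter: Se 0.80, Sp 0.50, LR+ 1.60 |
|---|---|---|
| 0.60 (1.500) | odds 1.688, PPV 0.63 | odds 2.400, PPV 0.71 |
| 0.65 (1.857) | odds 2.089, PPV 0.68 | odds 2.971, PPV 0.75 |

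The weak filter leaves both cases below 70%; the moderate one takes both above it.

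**Step 3: how informative the filter must be to reach 70%.** The target odds are 0.70/0.30 = 2.333. The LR+ needed is 2.333/1.857 = 1.26 from a PPV of 0.65, and 2.333/1.500 = 1.56 from 0.60. If staff lost no eligible family (Se = 1), this means removing 1 − 1/1.256 = 20% or 1 − 1/1.556 = 36% of would-be false positives.

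Se = 1 is the assumption most favourable to the concern. For example, at p = 0.55 with half the false positives removed, PPV is 0.55/(0.55 + 0.45×0.5) = 0.71. If 20% of true cases are lost as well, it is 0.44/(0.44 + 0.225) = 0.66.

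**Step 4: effect on the 70% comparison.** Assume 300 screened families. The binomial probability of observing at least 210 confirmed (70%) is 0.04 at a true PPV of 0.65 and 0.98 at 0.75. A moderate filter could thus decide the result, although the documents do not show that the filter would be of that strength.

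**Step 5: sensitivity.** The filter multiplies true sensitivity by Se, that is, by 0.90 or 0.80 in the cases above. It cannot raise it.

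**The case against.** The strongest reply is that no second filter is clearly intended. The pre-study section says ReachNow is used to find families eligible for the intervention and that a match prompts referral. The Recruitment section says recruitment uses ReachNow. Eligibility depends on the K10, the SDQ and structured questions, so it cannot be known before screening. On that view, families meeting the criteria is loose wording for ReachNow-positive families. This is a fair reading, but the text as it stands says otherwise and the training on the criteria is explicit, so it supports rewording rather than leaving the text alone.

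Other points reduce the likely size. The vignette already depicts mental health difficulties, family conflict and financial stress, so criteria knowledge may add little. Dropping a family for a severe condition may remove a reference-positive family rather than a false positive. A delivering organisation might also brief its own staff on whom the programme serves; in that case the estimate is valid for that package, provided the article says so.

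Three stronger readings are tempting and are not supported:

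- *That the 70% test is biased upward whatever the measure.* The hypothesis wording can be read as sensitivity, and sensitivity would fall if staff drop families. The upward direction holds for the PPV reading in Table 3.
- *That staff apply the tool knowing the reference result.* They know the criteria, not any family's result; research assistants administer screening afterwards. This is selection before verification, not full incorporation of the standard into the index test.
- *That a tool truly at 55% to 65% would pass.* It could, but only under assumed filters; weaker ones leave it below 70%.

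**Conclusion.** The point holds in a limited form. As written, the users of ReachNow are trained on the criteria that define the reference standard and contact families by those criteria before screening. The share of identified families confirmed at screening would therefore measure the tool plus an eligibility pre-filter, and would be raised to the extent that the filter carries information about eligibility.

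The size cannot be derived from the documents. Tool-only values of 0.60 to 0.65 becoming 0.63 to 0.75 are illustrations that rest on assumed filter properties and conditional independence. The conclusion also rests on taking the Recruitment sentence literally. It is worth acting on because it bears on a primary implementation hypothesis, the correction is cheap, and the lost information cannot be recovered after enrolment.

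**What to change.** 1. Have outreach staff record the ReachNow vignette decision for each family before making any eligibility judgement.
2. In *Recruitment*, replace "Outreach staff will contact families who meet the eligibility criteria" with a statement that staff contact families who are ReachNow-positive.
3. Refer all consenting ReachNow-positive families to the research assistants' screening, and leave the inclusion and exclusion criteria to that step. Base PPV on the recorded vignette decision.
4. Report ReachNow-positive families who are not screened, with reasons, as unverified. They have no reference result, so counting them as failures would bias PPV downward. With c confirmed among s screened and u unverified, give the range c/(s+u) to (c+u)/(s+u) beside the observed c/s.
5. If criteria training is meant to be part of the tool, define the index test as that package and limit the accuracy conclusion to it.

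The cost is one log field, a wording change, a small change to outreach training, and somewhat more screening interviews in families who turn out to be ineligible.

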##### Recruitment

Recruitment will be led by outreach staff under the supervision of War Child Jordan during the study enrolment period using the family version of the ReachNow detection tool. Outreach staff will contact families who meet the eligibility criteria, inform them about the intervention using a script and offer an invitation to participate. Those families who confirm interest will be asked for verbal consent and then referred to the research team for the screening assessment.

##### Informed consent and assent

Informed consent procedures will involve providing families with both oral and written information about the study. Trained research assistants will read the consent form to families and provide opportunities for questions. For families who agree to participate, signed consent will be sought from both caregivers where applicable (with an option for witnessed verbal consent), as well as verbal assent from participating children. Particular care will be taken to ensure understanding of voluntariness, and participants will be informed they can decline or withdraw from the study at any time without affecting their ability to participate in the intervention or receive services from the implementing organisations.

##### Screening

Screening assessments will be administered to caregivers by trained research assistants using tablets in private locations, with family members assessed one-by-one. The screening protocol will assess families for: caregiver mental health challenges (Kessler-10 [K10] ≥ 20); child mental health challenges (Strengths and Difficulties Questionnaire [SDQ] caregiver report ≥17); family relationship challenges (screening questions developed for study); caregiver parenting challenges (screening questions developed for study); financial stress (screening item developed for study); and absence of risks. One caregiver will be asked to report on children in the household. In households with more than three children, they will be asked to report on the children with the most severe emotional and behavioural challenges. Based on the caregiver-reported screening assessment for child mental health challenges, one index adolescent will be selected for subsequent data collection. If more than one child aged 10–17 years scores above the cutoff on the SDQ (≥17), the highest scorer will be selected as the index adolescent for the purposes of the study. Families who meet eligibility requirements will proceed to complete the baseline assessment. More details on the screening protocol, including cut-offs, can be found in Table 2 and Supplementary Document A.

**Table 2. tab2:** Screening protocol for study eligibility

Criterion	Inclusion criteria	Contextual validity
1a. Caregiver mental health	At least one caregiver scores ≥20 on the K10	Cut-off validated for detecting serious mental illness in general populations (Kessler et al., 2003) and feasibility study (⍺ = 0.85) (Brown et al., 2024)
1b. Child mental health challenges	At least one child scores ≥17 on the caregiver-report SDQ	Cut-off validated for detecting serious emotional and behavioural problems in general populations and acceptable internal consistency (⍺ = 0.73) in Arabic versions of parent- and teacher-report (Ababneh and Alomari, 2016; Emam et al., 2016; Al-Hendawi, 2023)
1c. Family relationship challenges	Structured screening questions were developed for this study and piloted in the feasibility study, assessing the presence of significant family conflict or dysfunction causing distress or impairment	Developed for context and validated in a feasibility study
1d. Parenting challenges	Structured screening questions were developed for this study and piloted in the feasibility study, assessing parenting difficulties causing significant distress or impairment	Developed for context and validated in a feasibility study
1e. Financial stress	Structured screening questions were developed for this study and piloted in the feasibility study, assessing family financial difficulties causing significant distress or impairment	Developed for context and validated in a feasibility study
2. Absence of severe risks requiring specialist care	Structured screening questions about serious concerns where at least one caregiver indicates potential for harm (*e.g.*, suicidality, severe substance abuse, active psychosis, ongoing family violence, *etc.*) Observed or reported challenges for any family member with suicidality, disordered thinking, severely impacted functioning, or other symptoms of serious mental health concerns, as well as serious protection concerns such as intimate partner violence, child abuse or coercion	Structured questions developed for context and validated in feasibility study Observation or disclosure during screening or data collection

##### Data collection

Research assistants will collect survey data from at least one caregiver and the index adolescent at baseline (T0: no more than 3 weeks before intervention), midline (T1: post-core modules), endline (T2: post-optional modules, within 3 weeks of the final session) and 6-month follow-up (T3). Surveys will collect sociodemographic information, outcome measures and hypothesised mediators (see below). After baseline, intervention families will be contacted to schedule sessions. Families discontinuing the intervention will be encouraged to complete the remaining assessments.

Research assistants will collect qualitative data using semi-structured guides after endline from a purposive subsample (*n* = 15) to examine implementation, effectiveness and potential sustainability. At least 10 families who completed the intervention and five who dropped out will be selected for interviews, ensuring representation across family composition, attendance and change in outcomes at T1 and T2. Focus group discussions (*n* = 4) and key informant interviews (*n* = 8) will be conducted with stakeholders from implementing organisations, including facilitators, supervisors and other staff, to explore implementation factors, programme sustainability and recommendations.

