### Trial design

The study is a single masked, two-arm RCT with an embedded qualitative process evaluation. Families will be randomised to the intervention or ETAU arms in a 1:1 allocation ratio. Outcomes will be assessed at baseline prior to randomisation (T0), at midline after the completion of core sessions (T1), at endline after the completion of advanced modules (T2, primary time point) and at follow-up 6 months after endline (T3).

The trial employs a sequential, dual outcomes approach to establish effectiveness through multiple pathways comparing treatment *versus* control conditions: (1) upstream improvements in family functioning, parenting practices or caregiver mental health in the full sample; (2) direct improvements in mental health in high-distress adolescents; or (3) enhanced protective effects of upstream improvements on adolescent mental health. Secondary exploratory analyses will examine mechanisms of change over time and the additive effect of the optional modules compared to core modules.

The embedded process evaluation will evaluate implementation, effectiveness and potential sustainability of core and optional modules through mixed methods, including surveys, programme monitoring, staff debrief meetings and qualitative interviews and focus groups. Qualitative activities will be conducted post-intervention (T2) with families who complete and drop out of the intervention, facilitators, outreach staff and other key personnel.

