#### Masking

All investigators and research assistants will be masked to the allocations of families. Due to the nature of the intervention, complete masking of participants and implementation staff is not possible. Staff will receive training on maintaining masking protocols during data collection, research and implementation teams will operate separately, and participants will be instructed not to reveal their allocation. Research assistants will document instances where allocation is accidentally revealed. The level of (un)masking of the research assistants will be assessed at the end of each follow-up interview by asking research assistants if allocation was explicitly revealed during the interview. These data will be used to assess the integrity of masking and to control for possible bias in impact analyses, in addition to being reported as a study limitation.

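### Research assistants declared masked without exception are also assigned to interview intervention completers and dropouts before T3, and nothing in the article keeps those interviewers from T3 assessment

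*Protocol article*

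**What the plan says.** The Masking section is unconditional: "All investigators and research assistants will be masked to the allocations of families". Its supporting measures are staff training, separation of the research team from the implementation team, an instruction to participants not to disclose their arm, a log of accidental disclosures, and a question at the end of each follow-up interview on whether allocation was explicitly revealed during it. These data are to be used to adjust for possible bias and reported as a limitation.

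The Data collection section gives one role two tasks. The first is the outcome surveys: "Research assistants will collect survey data from at least one caregiver and the index adolescent at baseline", and then at midline, endline and the 6-month follow-up. The second is the interviews: "Research assistants will collect qualitative data using semi-structured guides after endline from a purposive subsample", with n = 15. On who is interviewed it says: "At least 10 families who completed the intervention and five who dropped out will be selected for interviews", with the sample "ensuring representation across family composition, attendance and change in outcomes at T1 and T2". Four focus groups and eight key informant interviews "will be conducted with stakeholders from implementing organisations, including facilitators, supervisors and other staff".

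On timing, the Trial design section says: "Qualitative activities will be conducted post-intervention (T2) with families who complete and drop out of the intervention". The same section puts T3 six months after endline and names T2 as the primary time point.

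**The concern.** A family described as having completed or dropped out of the intervention can only be in the intervention arm. Whoever interviews it knows the arm from the selection alone, and again from the topics, which are implementation, effectiveness and sustainability. The plan gives this task to a role that it also declares masked throughout, so the two statements cannot both be true.

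What is at stake is the T3 assessment. If an interviewer later administers the T3 survey to the same family, that assessment is unmasked. All the families concerned are in one arm, so any influence on their answers has no counterpart in the control arm.

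The existing masking check would not reliably show this. A research assistant who learned the arm in an earlier qualitative interview can truthfully answer at T3 that nothing was revealed in that session. The family would then count as masked in the adjustment that the plan intends.

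**Working it through.** The plan states no figure on this point. The check compares the sections and then sizes the exposure.

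**Comparison of the sections**

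| Question | Protocol article | Section |
|---|---|---|
| Who is masked? | All investigators and all research assistants, no exception | Masking |
| Who collects T0–T3 surveys? | Research assistants | Data collection |
| Who interviews families? | Research assistants | Data collection |
| Which families? | Intervention completers and dropouts only | Data collection; Trial design |
| When? | After endline, placed at T2 | Data collection; Trial design |
| When is T3? | Six months after endline | Trial design |
| Are interviewers separated from T3 assessors? | Not stated; only research and implementation teams are separated | Masking |
| What does the check ask? | Disclosure during that follow-up interview | Masking |

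The interviews come after endline and before T3. The interval is therefore up to six months; no exact date is given. For the interviewed families, the T2 data are already collected when the interview takes place.

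**Share of families exposed**

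Inputs: 15 interviewed families (Data collection); 550–600 families recruited and 20% attrition (Sample size); 1:1 allocation (Trial design).

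- Of all families: 15/550 = 2.7%; 15/600 = 2.5%.
- Of the intervention arm as randomised: 15/275 = 5.5%; 15/300 = 5.0%.
- Of the intervention arm after 20% attrition, if all 15 are seen at T3: 15/(0.8 × 275) = 15/220 = 6.8%; 15/(0.8 × 300) = 15/240 = 6.3%.

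**Possible shift in the T3 arm difference**

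Let b be the shift in SD units in an interviewed family's T3 score caused by an unmasked assessor. The documents give no value, so 0.2–0.5 SD is assumed. With no exposed families in the control arm:

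shift in arm difference = b × (exposed families / families in the arm)

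- b = 0.2: 0.2 × 15/275 = 0.011 SD; 0.2 × 15/220 = 0.014 SD.
- b = 0.5: 0.5 × 15/275 = 0.027 SD; 0.5 × 15/220 = 0.034 SD.

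Against the minimum effect of d = 0.15 in the Sample size section, this is 0.011/0.15 = 7% to 0.034/0.15 = 23%. The calculation assumes that each of the 15 families is assessed at T3 by someone who knows its arm from the interview. Any reassignment lowers the figure towards zero.

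**The case against.** A reader might infer that the plan unmasks its own outcome assessors. The article does not show this. It names a role, not individuals, and nowhere says that the person who interviews a family will later assess it, or do any T3 survey. A condensed article may leave staff rostering to the full protocol. This objection stands against the claim of a demonstrated breach. It does not rescue the masking statement: even with separate individuals, the interviewers are research assistants, and research assistants are all said to be masked.

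A reader might also infer that sampling on attendance and outcome change forces masked staff to see arm-revealing data. The article does not say who draws the sample. Attendance comes from programme monitoring, and a masked person could supply change scores without seeing the arm. The stronger inference is unsupported; the point only needs stating.

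A third inference would be that the trial's main result is at risk. It is not: T2 is primary, the interviews of these families follow endline, H1 is tested at T2, and H3 is declared exploratory and also uses T2.

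The Masking section does record and adjust for unmasking. That is a real safeguard, but it is framed around accidental disclosure and disclosure within the follow-up interview, whereas here the knowledge is planned and comes earlier.

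Finally, the outcomes are self- or proxy-reports from respondents who are not masked, so an assessor's knowledge may add little to the reporting bias already present. That is fair, and it supports treating the point as minor. Nor does exposure in one arm fix the sign of any bias: five of the 15 families are dropouts.

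**Conclusion.** The contradiction holds. As written, the claim that all research assistants are masked is untrue for those who interview intervention families, nothing in the article stops them from assessing T3, and the masking check could miss what they already know. The consequence is small and confined to T3 outcomes and the T3 part of exploratory H3. It concerns about 5–7% of the intervention arm, with a possible shift of about 0.01–0.03 SD in an unknown direction. That range rests on the assumed 0.2–0.5 SD shift and on interviewers carrying out the T3 assessments of all 15 families. Focus groups and interviews with facilitators could reveal the arm of further families if research assistants run them, but the documents do not allow a count. This is a low-cost improvement, not a threat to the primary analysis.

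**What to change.** - Bar any research assistant who conducts family interviews from T3 assessment of at least the families they interviewed, and preferably from all T3 assessments. Apply the same rule to those who run the focus groups and interviews with facilitators. Alternatively, hold each family's interview after its T3 assessment.
- Have the purposive sample drawn by someone outside the masked team, with masked staff supplying outcome changes only.
- In the Masking section, limit the statement to outcome assessors and name the qualitative interviewers as the exception.
- Extend the masking check so that it asks whether the assessor knew the allocation from any source before the interview, as well as whether it was revealed during it.

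The cost is rostering of existing staff, a few sentences of protocol text and one more question on the masking form. The downside is less scheduling flexibility. If the interviews are held after T3 instead, families will be recalling the programme from further back. Recruitment was due to start in December 2025 and the interviews come only after endline, so the change affects a late step of the study.
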